### Data management and statistical analysis

Clinical data is manually registered using a paper Case Report Form (CRF). CRF data is entered in the study database using an Electronic Data Capture (EDC) system. After double data entry, resolution of all inconsistencies, and coding by means of medical dictionaries, a final quality control process will be applied. In case of compliance, the database will be considered error free and will be frozen for the statistical analysis of the data. Sponsor and investigator will have access to the final trial dataset.

A descriptive analysis will be performed including all demographic variables collected, as well as baseline clinical data. Qualitative variables will be summarized using absolute frequencies and percentages, while quantitative variables will be described using the mean, median, standard deviation, maximum, minimum and number of observations.

The efficacy evaluation of quantitative parameters will be performed by comparing basal values (prior to the administration of the product) with those recorded in the follow-up visits, using the paired Student’s t-test (if the variable meets the normality requirements), or the Wilcoxon paired test for all other cases. For qualitative parameters, the Chi-square test will be used.

Two interim analyses will be performed during the study. The first one, to ensure the statistical power of the study, will be performed when the first 20 patients reach a minimum follow-up of 6 months, and will include a new sample size calculation based on these data. In the second one, the main variable under study will be analysed once 6-months of follow-up have been completed in all patients recruited. If the results are positive, patients randomised to the control group will be treated via compassionate-use basis with their own cryopreserved BMMNCs, as early mentioned. Per-protocol analysis (PPA) will be used for all efficacy assessments. All p-values and confidence intervals will be calculated and evaluated using a 95% two-sided confidence level.

Safety analysis is aimed at estimating the number and percentage of patients dropped out due to AEs, the number of patients who have experienced at least one AE, the most frequent AEs and the number of patients who experienced at least one SAE. The 95% confidence intervals will be also determined. Safety evaluation will be performed with intention-to-treat analysis.

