Different experimental studies in animal models of DC have shown improvements in ejection fraction and decreases in the ventricular volumes after cell therapy [12–21]. These benefits have also been established in clinical studies aimed at analysing the safety and efficacy of bone marrow-derived progenitor cells in patients with DC [22–31]. In 2006, the ABCD trial [26] described for the first time in humans improvements in the NYHA functional class, a decrease in end-diastolic volume and an average improvement of 5.4% in the ejection fraction in 24 patients with DC treated with intracoronary BM-derived cells. A long term follow-up of this trial showed that the functional benefits achieved were maintained without late adverse effects [25]. Similarly, Fischer-Rasokat et al. [23] observed in 33 patients with DC that intracoronary administration of BM-derived cells appears to be associated with improvements in cardiac contractile and microvascular function in patients with DC (ref). More recently, these results have been confirmed by the REGENERATE-DCM clinical trial [30], in which a 5.37% increase in left ventricular ejection fraction (LVEF) was observed at 3 months after treatment with autologous BM-derived cells combined with peripheral granulocyte colony-stimulating factor (G-CSF). Next to these previous experiences, our group has completed a one-year Phase II Clinical Trial (NCT00629096, EudraCT 2007–003088-36) to evaluate the safety and efficacy of intracoronary infusion of autologous BMMNCs in 27 patients with DC [32]. In this study, an improvement in the New York Heart Association (NYHA) functional class and a reduction of brain natriuretic peptide (BNP) plasma levels were observed without any adverse effect. In addition, a significant decrease in ventricular volumes along with a mean increase in the ejection fraction of 9% in 20 out of the 27 patients was observed at month 6. These changes suggest a favourable effect of cell therapy on ventricular remodelling, which may explain the decrease (or even disappearance) of the degree of mitral regurgitation observed in some patients. However, the gain in ejection fraction after cell therapy varied greatly between patients, ranging from − 9% to + 34%, being this gain greater in patients with a baseline ejection fraction < 25%. The clinical benefit of cell therapy was stable 5 years after infusion, with 69% survival rate and 43% of patients free of major events, staying within a NYHA functional class of I-II [33]. Interestingly, younger patients seemed to show the highest long term response to cell-based therapy in terms of LVEF improvement. However, contradictory reports have been published which show no improvements in ejection fraction, NYHA functional class, or exercise test outcomes after intracoronary infusion of autologous BMMNCs in patients with DC [29]. However these findings should be interpreted with caution as, despite apparent similarities, important methodological differences exist among published reports: BMMNCs dose, LVEF measuring technique, administration procedure, clinical description of eligible patients, subject follow-up length, use of G-CSF, technique of bone marrow cell harvesting etc. Ultimately, clinical studies using BM-derived cells in DC patients have shown only modest benefits [34–36]. We believe that the proposed clinical study may contribute with a new methodological perspective on search for cell therapy-based treatment alternatives in patients with DC. In summary, there is sufficient preliminary evidence to consider intracoronary injection of BMMNCs as a viable, safe and beneficial treatment in patients with DC. However, there is a need for larger, randomized, controlled studies to understand the biological mechanism of action of BMMNCs in the myocardium and the factors affecting clinical response to regenerative therapy with autologous BMMNCs in patients with DC.

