### Sample size calculation

A sample size calculation was performed based on the clinical trial study already completed by our group [32]. In this study, a mean increase in ejection fraction of 9.4 ± 9.9% was observed. At the end of the follow-up, mean values of LVEF were 38% among responders, and 27% among non-responders. The sample size calculation was done using GRANMO (v7.12) for paired or repeated measures in two groups. Accepting an alpha risk of 0.05 and a beta risk of 0.2 in a two-sided contrast, 17 subjects are required in the first group and 34 in the second one to detect a difference equal to or greater than 9 units. It is assumed a common standard deviation of 10 and a correlation coefficient between the initial and final measurement of 0.5. A loss to follow-up rate of 10% has been estimated. However, an interim analysis has been planned in order to re-calculate trial sample size based on the mean increase in ejection fraction observed in the first 20 patients that complete a 6 months’ follow-up period.

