### Randomisation and blinding process

Randomisation is centrally performed by the sponsor, stratified by age (> or ≤ 45 years old) in a 2:1 block randomisation allocation BMMNCs or placebo. As sample size is small and both planned interim analysis may require a balanced distribution of the subjects within both study groups, block randomization is applied. Randomization list was computer generated by the Sponsor, and allocation is kept concealed for the research teams recruiting patients.

Investigators and patients (as well as clinical monitors) are blind to the treatment assigned. In the case of SAE, when the patients’ management could be improved by the knowledge of the blinded treatment assigned, the principal investigator may request the sponsor formal permission for subject unblinding. Additionally, specific unblinding of patients allocated to the control group may be authorized by the sponsor to allow for the treatment through compassionate use with their own previously cryopreserved BMMNCs.

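### The only test named for the primary LVEF endpoint is a within-patient paired test, which conflicts with the placebo comparison that the trial is designed and sized for

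*Protocol article*

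**What the plan says.** All references are to the protocol article.

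- **Data management and statistical analysis.** After a paragraph on descriptive summaries, the efficacy evaluation of quantitative parameters is defined as "comparing basal values (prior to the administration of the product) with those recorded in the follow-up visits, using the paired" t-test, with the Wilcoxon paired test as the non-normal alternative. For categorical data it says: "For qualitative parameters, the Chi-square test will be used". It does not say which groups the chi-square compares. The section also provides that, if the second interim analysis of the main variable is positive, control patients will receive their own stored cells. Positive is not defined.
- **Study outcomes** and **Angiographic measurement of ventricular function.** The primary endpoint is the change in angiographic LVEF between the infusion visit and month 6, a quantitative variable.
- **Abstract (Methods), Trial design and Discussion.** The trial is described as a randomised, double-blind comparison of functional recovery against placebo.
- **Sample size calculation.** With two-sided alpha 0.05 and power 80%, the section concludes that "17 subjects are required in the first group and 34 in the second one to detect a difference equal to or greater than 9 units". The other inputs are given as a "common standard deviation of 10 and a correlation coefficient between the initial and final measurement of 0.5", plus 10% loss to follow-up. The software option is described as being for paired or repeated measures in two groups.
- **Randomisation and blinding process.** Allocation is "stratified by age (> or ≤ 45 years old) in a 2:1 block randomisation allocation".
- **Background and rationale.** The pilot's LVEF gain varied widely between patients, "being this gain greater in patients with a baseline ejection fraction < 25" percent.

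**The concern.** A paired test asks whether patients changed. The randomised question is whether BMMNC patients changed more than placebo patients. Anything that moves LVEF in both arms, such as repeat-measurement effects or further adjustment of medication during follow-up, counts towards significance in the paired test and cancels in a between-arm test.

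This is not a detail left for an analysis plan. The article names a specific test, and that test does not fit the design or the sizing. Comparing the two arms' paired p-values does not repair it: significance in one arm and not in the other is not a test of the difference, and with 2:1 allocation the larger BMMNC arm reaches significance more easily for the same true change.

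Two things depend on this: the trial's efficacy claim, and the finding at the second interim analysis that bears on releasing stored cells to placebo patients. As the text stands, both could rest on change that has nothing to do with the cells.

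**Working it through.** **1. Reproducing the plan's sample size.** Inputs from the sample size section: difference 9, SD 10, pre-post correlation 0.5, two-sided alpha 0.05, power 80%, ratio 2:1, loss 10%.

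- SD of change = 10 × √(2 × (1 − 0.5)) = 10.
- Smaller group, two-sample comparison of change: n = (1.96 + 0.842)² × 10² × (1 + 1/2) / 9² = 14.5, rounded up to 15. The larger group is 30.
- Allowing for loss: 15/0.9 = 16.7, up to 17; 30/0.9 = 33.3, up to 34. Total 51.

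This matches the stated "17 subjects are required in the first group and 34 in the second one to detect a difference" exactly. The trial is therefore sized for a between-arm difference in change. A one-group paired test with SD of change 10 needs only about 12 patients to detect 9 points (power 77% at 11, 81% at 12), so the test in the analysis section is not the one that gives 51.

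**2. What the named test does when treatment has no effect.** Assumptions: 30 BMMNC and 15 placebo patients evaluable, SD of change 10 in both arms, and the same true gain in both arms. The article gives no placebo change, so the common gain is an assumption and is shown as a range. The article also does not say whether the paired test is run by arm; it is taken here within each arm.

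For a common gain *m*, the paired t statistic in an arm of size *n* follows a noncentral t distribution with *n* − 1 degrees of freedom and noncentrality *m*/(10/√*n*). Let *a* be the probability of p < 0.05 in the direction of improvement with n = 30, and *b* the probability of p < 0.05 in either direction with n = 15. The arms are independent, so the probability that BMMNC is significant and placebo is not is *a*(1 − *b*).

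| Common gain (LVEF points) | *a*: BMMNC significantly positive | *b*: placebo significant | *a*(1 − *b*) |
|---|---|---|---|
| 0 | 2.5% | 5.0% | 2% |
| 1 | 8% | 7% | 7% |
| 2 | 18% | 11% | 16% |
| 3 | 36% | 19% | 29% |
| 4 | 56% | 30% | 39% |
| 5 | 75% | 44% | 42% |

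A valid two-sided 5% between-arm test would favour BMMNC falsely in 2.5% of trials in every row.

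**3. What a between-arm test gives at the same sample size.** Power for a 9-point difference, two-sided 5%, noncentral t:

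- Change-score t-test, SD 10. The standard error is 10 × √(1/15 + 1/30) = 3.16 at 30/15 and 10 × √(1/17 + 1/34) = 2.97 at 34/17. Power is 79% and 84%.
- ANCOVA on baseline LVEF, residual SD = 10 × √(1 − 0.5²) = 8.66. Power is 89% at 30/15 and 93% at 34/17.

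No extra patients are needed under either test.

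**The case against.** The best defence is that the comparison with placebo is clearly intended. Three sections state it, and the sample size is built on it. That section also uses the word paired for a two-group method, so the analysis paragraph may be a clumsy condensation of a between-arm comparison of paired changes. The article is a summary, and a fuller protocol or analysis plan may be correct. This stands as far as intent goes: a reader might infer that the trial never compares the arms, and the article does not support that. It does not rescue the paragraph, which is headed as the efficacy evaluation, is separate from the descriptive analysis, names paired tests and no other for quantitative parameters, and is followed by a rule for p-values and confidence intervals.

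Other limits also stand:

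- **Chi-square.** A reader might infer that it treats baseline and follow-up readings on the same patient as independent. The text does not say that; a comparison between arms is an equally natural reading. The sentence is unclear, not shown to be wrong.
- **Regression to the mean.** Low LVEF at entry suggests it, but entry uses a screening echocardiogram while the tested baseline is a separate angiogram at the infusion visit. Selection is not on the tested value. Six months of optimised medication before inclusion also limits drift, without excluding it.
- **Size of the common gain.** It is assumed. At 0 or 1 point the inflation is nil or modest.
- **Covariates.** A two-sample test of change would be valid. Adjustment for baseline LVEF and age is an improvement, and its absence from an article is not an error.
- **Compassionate use.** Release is not automatic: the trial design section speaks of conclusive evidence allowing authorisation, and an independent committee advises on statistical issues.

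**Conclusion.** The point holds for quantitative efficacy parameters, including the primary endpoint. The only test named is within patients, and it contradicts the placebo-controlled design and the two-group sizing. The article's undefined positive result could therefore rest on change common to both arms.

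With no treatment effect, the chance of a significant improvement in the BMMNC arm runs from 2.5% with no common gain to 75% with a common gain of 5 points. Reading BMMNC significant with placebo not significant as success gives 2% to 42%. These rates assume SD of change 10, 30 and 15 evaluable patients, and a paired test applied by arm. The common gain is not in the document, so no single figure in the range can be called the trial's error rate.

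It would go too far to conclude that the design or the sample size is at fault. The 17 and 34 are right for the comparison the trial intends; the error is in the analysis text. Because the primary inference depends on that text, it must be corrected.

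**What to change.** Replace the efficacy paragraph so that it states:

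1. **Primary analysis.** Month-6 angiographic LVEF compared between BMMNC and placebo, preferably by ANCOVA with baseline angiographic LVEF and age stratum (≤ 45 or > 45 years) as covariates, reporting the adjusted difference, 95% confidence interval and two-sided p-value. A two-sample test of change is an acceptable but less powerful alternative.
2. **Positive result.** The efficacy result called positive at the second interim analysis is defined by that between-arm test. What clinical action follows is for the sponsor and the authorities and is not addressed here.
3. **Within-arm changes.** Paired changes from baseline are reported as description only.
4. **Qualitative parameters.** The chi-square test compares the arms.

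The sample size stays at 51, and no new data are needed: baseline angiographic LVEF and age are already collected. The cost is a wording change, but it has to pass as a protocol amendment, because the ethics section requires authorisation by the Ethics Committee and the medicines agency for any modification. It should be settled before the comparative results of the second interim analysis are seen.

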## Methods and design

### Trial design

The study is designed as randomized, placebo-controlled, double-blind phase IIb clinical trial to compare the functional recovery of patients receiving the conventional treatment for DC in combination with an intracoronary infusion of BMMNCs, using placebo as a control. A 2:1 BMMNC/placebo allocation ratio is used for the randomization of a total of 51 eligible patients. Therefore, a total of 34 subjects will receive BMMNCs infusion, whereas 17 subjects will be treated with a placebo infusion. In order to analyse the predictors of clinical response as well as safety variables, all trial subjects (*n* = 51) are followed for a period of 24 months, completing a total of nine study visits: screening (visit 1), randomization (visit 2), infusion (visit 3), 24 post-infusion (visit 3.1), and months 3 (visit 4), 6 (visit 5), 12 (visit 6), 18 (visit 7) and 24 (visit 8) after the BMMNC/placebo administration (Fig. 1). To allow for sample size re-calculation an interim analysis will be performed with the data from the 6 months post-infusion period of the first 20 patients included. A second interim analysis is planned when the last patient included in the trial has completed study visit 5 (6 months). This early analysis of the data may provide conclusive efficacy (and safety) evidence in order to allow for the authorization of compassionate treatment of finalized patients allocated to placebo. On-completion of protocol standardized 24 months’ follow-up, all patients receiving the experimental treatment will be followed on an observational scheme for an additional period of up to 5 years. This extended follow-up period will provide long term efficacy and safety data of BMMNCs infusion.

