LVEF improvement is the main study variable, and it will be evaluated angiographically by an expert angiographer blinded to treatment allocation and patient’s progression. Although this technique is not the gold standard for LVEF estimation, the approach will reduce inter-observer variability and provide more accurate, repeatable results, avoiding some of the limitations of echocardiographic estimates. Cardiovascular Magnetic Resonance (CMR) was not a feasible option in the context of this study due to the high frequency of devices (Cardiac Resynchronization Therapy Defibrillator or CRT-D) in this population that interfere with CMR scans results. Also, not all participating sites had equivalent CMR techniques, which may have provided LVEF estimates based on non-comparable images, leading to increased variability of results. Consequently, the main limitation of the present trial design is its comparability across studies that measure LVEF using magnetic resonance imaging.

In order to reduce the risks of left ventricular angiography, only two assessment points are stablished throughout follow-up (at baseline and 6 months after treatment). Also, the risk of contrast-induced acute kidney injury is minimized by the exclusion of patients with serum creatinine higher than 2,5 mg/dL. However, as the moment of highest benefit (if any) after cell infusion is still unclear, complementary non-invasive measurements of LVEF using 2D echocardiography are set out at baseline, as well as at months 3, 6, 12, 18 and 24 after treatment. Although both estimates will not be interchangeable, a correlation may be stablished that will allow for drawing conclusions about the long and short-term effects of BMMNC.

In conclusion, the results of the present trial are expected to envision a new therapeutic alternative for the treatment of idiopathic DC. Current pharmacological treatments aim to improve blood flow and prevent further damage to the heart, but they are not curative. Stem cell therapy constitutes a promising alternative to palliative care, restoring cardiac structure and function. Once the safety and efficacy of this advanced therapy product is established in humans, the final goal will be to confirm these observations in future phase II and/or phase III clinical trials involving a larger number of subjects.

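### Paired baseline-to-visit tests do not compare the arms; the repeated secondary outcomes need one between-arm repeated-measures model

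*Protocol article*

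**What the plan says.** Under Data management and statistical analysis, quantitative efficacy parameters are evaluated by "comparing basal values (prior to the administration of the product) with those recorded in the follow-up visits", with the paired Student's t-test or, if normality fails, the Wilcoxon paired test. The section names no other method for quantitative outcomes.

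Echocardiographic LVEF is a secondary outcome with several follow-up values. The section on echocardiographic measurement lists baseline and months 6, 12, 18 and 24. The Discussion adds month 3: "complementary non-invasive measurements of LVEF using 2D echocardiography are set out at baseline, as well as at months 3, 6, 12, 18 and 24". It gives the reason for the series: the time of greatest benefit is not known, and short- and long-term effects are to be described. Natriuretic peptide and exercise testing are also secondary outcomes; their visit schedule is in Fig. 1.

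The primary outcome, angiographic LVEF, is measured only twice, on the day of infusion and at month 6.

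The sample size rests on a comparison of two groups: "17 subjects are required in the first group and 34 in the second one to detect a difference equal to or greater than 9 units". Control patients may later receive their own stored cells if the second interim analysis is positive.

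**The concern.** The trial is randomised and placebo-controlled, and its size was set for a difference between arms. The named test looks at change from baseline within patients. Change over time mixes any treatment effect with natural course, adjustment of background treatment, regression to the mean and placebo response. A significant rise in the cell arm is therefore not evidence that the cells caused it.

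For the repeated secondary outcomes there are two further losses. Each test uses two values per patient and ignores the other visits. A patient without a value at, say, month 24 drops out of that test even when months 6 to 18 were recorded. The article itself expects some loss: "A loss to follow-up rate of 10% has been estimated".

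At stake are the statements about short- and long-term effect that the Discussion expects the echocardiographic series to support.

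**Working it through.** **Inputs.** From Sample size calculation: "Accepting an alpha risk of 0.05 and a beta risk of 0.2 in a two-sided contrast"; "It is assumed a common standard deviation of 10 and a correlation coefficient between the initial and final measurement of 0.5"; 10% loss; a 9-unit design difference. From Trial design: "A 2:1 BMMNC/placebo allocation ratio is used for the randomization of a total of 51 eligible patients". The illustrative effect of 5.4 units comes from Background and rationale, which reports "an average improvement of 5.4% in the ejection fraction in 24 patients with DC". It is a change in treated patients of another trial, used here only as a plausible size. The correlation r between follow-up visits is not in the article; I assume 0.5 to 0.9.

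**The plan's own figure.** SD of change = 10 × √(2 × (1 − 0.5)) = 10. Smaller group at 2:1: 1.5 × (1.96 + 0.8416)² × 10² / 9² = 14.5, so 15, with 30 in the other. Dividing by 0.9 gives 16.7 and 33.3, so 17 and 34. The stated size reproduces, and it does so as a between-arm comparison. At 15 v 30 evaluable, a two-sample t-test of change has 79% power for 9 units.

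**The named test.** Within-arm paired t-test, non-centrality = rise / (10/√n), two-sided 5%:
- Active arm, n = 30, rise 5.4: 5.4 / 1.826 = 2.96, power 81.6%.
- Placebo arm, n = 15, rise 5.4: 5.4 / 2.582 = 2.09, power 49.5%.

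If both arms rise by 5.4, the true treatment difference is zero, yet the active-arm test is significant 81.6% of the time. The pattern of active significant and placebo not significant arises with probability 0.816 × (1 − 0.495) = 41%, from the unequal arm sizes alone.

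**Between-arm comparison at one visit, 5.4 units, 15 v 30.** The factor √(1/15 + 1/30) is 0.316.
- Change score: SD 10, SE 3.16, non-centrality 1.71, power 38.6%.
- Baseline-adjusted: SD 10 × √(1 − 0.25) = 8.66, SE 2.74, non-centrality 1.97, power 48.7%.

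This is all the primary outcome can gain, because it has one post-baseline value.

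**Average over four echocardiographic visits (months 6 to 24), baseline-adjusted.** Variance = 100 × [(1 + 3r)/4 − 0.25]. The effect is constant at 5.4, or fades as 5.4, 4, 3, 2 (mean 3.6). Power is from the non-central t with 42 degrees of freedom.

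| r | Variance | SD | Power, constant effect | Power, fading effect |
|---|---|---|---|---|
| 0.5 | 37.5 | 6.12 | 77.8% | 44.3% |
| 0.7 | 52.5 | 7.25 | 63.4% | not calculated |
| 0.8 | 60.0 | 7.75 | 57.7% | 30.1% |
| 0.9 | 67.5 | 8.22 | 52.8% | not calculated |

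With month 3 as a fifth visit, the constant-effect figures are 80.5% at r = 0.5 and 58.4% at r = 0.8.

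**Natriuretic peptide and exercise test.** The article gives no SD or correlation for these, so no power figure can be calculated.

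**The case against.** A reader might infer that each planned test is weak, and that a longitudinal model would lift power from 39% to 58-78% for LVEF, natriuretic peptide and exercise alike. The documents do not support that.
- The 39% belongs to a between-arm comparison of change scores, which the analysis section does not name. The paired test it does name has 82% power for a 5.4-unit rise in the active arm. Its fault is what it tests.
- The step from 39% to 49% comes from baseline adjustment at a single visit. Only the step from 49% upwards comes from the extra visits.
- The gain needs a constant effect, while the Discussion says the time of greatest benefit is unclear. Under the fading pattern the average does worse than a single adjusted month-6 test (30-44% against 49%). With complete data, the model's contrast at any one visit stays near 49%.
- The SD and correlation come from the primary calculation, and the article says that LVEF techniques are generally not interchangeable. The trial is sized for 9 units, not 5.4.
- Later treatment of controls with their own cells could dilute the late contrasts.

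All of this stands and limits the power claim.

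It can also be said that the trial's stated purpose is to compare the arms, and that an article leaves covariance structure and missing-value handling to an analysis plan. The second point is fair, and nothing here rests on those details. The first does not remove the problem: the article states a method for quantitative outcomes, and that method has no between-arm test. An analysis plan that followed it would inherit the fault.

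**Conclusion.** The concern holds in a limited form. The stated tests do not estimate the treatment effect on the repeated secondary outcomes, they ignore a patient's other visits, and they lose patients with a missing value at the visit tested. The first fault is the gravest: 82% apparent success in the active arm with no true difference, if both arms rise by 5.4 units with SD of change 10 and 30 evaluable. A smaller common rise gives less (36% for 3 units, 19% for 2 units).

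The gain in precision is secondary, conditional and limited to echocardiographic LVEF: 49% to between 53% and 78%, for r from 0.9 down to 0.5. It assumes that SD 10 and correlation 0.5 carry over from the sample-size calculation, that a 5.4-unit difference is constant from month 6 to 24, and that later treatment of controls causes no dilution. For the primary outcome, the corresponding point is a baseline-adjusted comparison between arms at month 6, with no contribution from extra visits.

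**What to change.** - For echocardiographic LVEF, natriuretic peptide (log scale) and the exercise measures, fit one repeated-measures model per outcome with arm, visit, arm-by-visit, baseline value and age stratum. Report the between-arm contrast with its confidence interval at each visit. Add one average over visits, named in advance, as a supporting summary.
- For month-6 angiographic LVEF, name a between-arm comparison adjusted for baseline.
- Keep the paired tests as descriptive statements of change within each arm.
- State how values recorded after compassionate-use treatment of control patients enter the analysis. Trial design speaks of control patients who have finalized, while the statistical section sets no such limit; the two passages must be reconciled.
- Settle whether echocardiography is done at month 3, so that the visits in the model are fixed.
- If a power gain is quoted, give it for echocardiographic LVEF only, with its assumptions.

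The cost is revised analysis wording and slightly more programming, with no new visits or data. The one downside is that the average loses power if the effect fades, which is why the per-visit contrasts must be kept. The model keeps patients with some missing visits, on the assumption that values are missing at random.
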